**Fig. 1 Fig1:**
[figure not shown]
Schematic of study design. ICH, intracerebral hemorrhage; IV, intravenously

### Follow-Up Time

At each study site, trained research coordinators blinded to treatment assignments will perform follow-up visits and calls. Follow-up clinic visits will be done at 30 ± 3 days and 180 ± 14 days after drug last dose. Follow-up phone calls will be done at 90 ± 3 days after drug last dose.

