### Study Intervention

The intervention will start within 24 h of symptom onset in the intensive care unit or hospital ward (Fig. 1). Participants will be monitored daily throughout the treatment phase (randomization through day 5 or discharge if sooner) and will receive guideline-based usual care treatment for the duration of the study. Usual care treatment will follow American Heart Association guidelines for the management of ICH [26]. Participants will receive either MW189 (0.25 mg/kg) or saline administered IV over approximately 20 min every 12 ± 2 h for up to 5 days (10 doses) or until discharge, whichever comes first. University of Iowa Pharmaceuticals, an FDA-registered pharmaceutical contract manufacturing organization, prepared the MW189 drug product. It is a sterile concentrated solution in 0.9% sodium chloride at 2.5 mg/mL with a pH of roughly 2.4 that is diluted in saline prior to IV administration. The concentration of the diluted solution must not exceed 0.4 mg/mL, which will confirm that the minimum solution pH is 3.0. At a dose of 0.25 mg/kg and a diluted solution concentration of 0.4 mg/mL, the volume for a 50- to 120-kg adult will be 31–75 mL over a 20-min infusion time. Participants randomized to placebo will receive 0.9% sodium chloride, USP (US Pharmacopeia), at a volume equal to that of the active treatment as calculated based on the participant’s weight.

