### Study Outcomes

The primary study outcome is the proportion of deaths from all causes during the first 7 days post randomization. Secondary outcomes include all-cause mortality at 30 days, hematoma expansion and recurrent ICH, brain infection, standard pharmacokinetic parameters (time to maximum plasma concentration [*T*_max_], *C*_max_, area under the curve, half-life [*t*_1/2_], clearance [CL], volume of distribution during terminal phase [*V*_z_], apparent terminal elimination rate constant [λ_z_]) determined at different times after MW189 administration, radiographic measures of edema during treatment and at the end of treatment for days 1–5, and measures of plasma and cerebrospinal fluid inflammatory and neuronal injury biomarkers during treatment and at the end of treatment for days 1–5. We will use a semiautomated threshold approach (range 44–100 Hounsfield units) to determine hematoma volume. Significant hematoma expansion will be defined as an increase between baseline and any follow-up CT scan of > 6 mL or > 33%. IVH volume will not be included in hematoma expansion. Recurrent ICH refers to the emergence of a new ICH following an initial episode of spontaneous ICH. It is subsequent spontaneous bleeding in the brain distinct from the initial event, typically occurring after a time frame of around 30 days or more. This is different from ICH expansion, which involves the enlargement of the initial bleed without the occurrence of a completely new bleeding event. Brain infection refers to infection present within the brain tissue and is evaluated based on the clinical symptoms, laboratory test results, and imaging findings. Radiographic measures of edema refer to the quantitative assessment of PHE and will be analyzed via both CT and magnetic resonance imaging (MRI) scans using semiautomated volumetrics with OsiriX software to compare the volume of edema between the two treatment groups. The primary imaging outcomes are absolute PHE and relative PHE and edema extension distance measured on brain CT scans performed at admission and at day 5 of the infusion. PHE measurements on MRI will be performed on the subset with MRI at baseline and at the end of the study. Group differences in edema volumes will be compared.

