Exploratory end points include clinical and functional outcomes collected at days 30, 90, and 180 (assessed using dichotomized modified Rankin Scale scores of 0–3 vs. 4–6, the National Institutes of Health Stroke Scale, the Montreal Cognitive Assessment, the Barthel Index, the Stroke Impact Scale, and the Center for Epidemiologic Studies-Depression scale) and participant status at 180 days from ICH, including serious AEs, AEs of special interest, hemorrhage expansion and recurrent ICH, infections, and mortality.

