### Statistical Analyses

The intention-to-treat analysis set (all randomized participants) will be used for efficacy analysis. All participants who receive any study treatment will be included in the safety analyses. Continuous variables of normal distribution will be expressed as mean ± standard deviation, whereas continuous variables of nonnormal distribution will be expressed as median and interquartile range. Categorical variables will be represented as frequencies and percentages. We anticipate no missing data for the primary outcome, as all-cause mortality within 7 days of treatment initiation is verifiable.

The primary outcome will involve an estimate of the difference in the proportion of all-cause mortality within 7 days of treatment initiation using a 90% one-sided confidence interval on the upper bound of this difference. The null hypothesis will be rejected if this confidence interval is less than 10%. In addition, we will also estimate the treatment difference in the proportion of 7-day all-cause mortality using a multivariable logistic regression model. This model will consider age, sex, race and ethnicity, ICH volume at stability, Glasgow Coma Scale (GCS) score, presence of IVH, withdrawal of life-sustaining therapy, and ICH location (deep versus lobar). This trial encompasses infratentorial ICH, which comprises brainstem ICH classified as deep location and cerebellar ICH classified as lobar location. Age, sex, and race and ethnicity data are collected at the screening visit. The GCS score is measured at baseline. Presence of IVH and ICH location are determined based on the diagnostic CT scan. The ICH volume assessed on the stability CT scan determines the need for additional imaging to establish hematoma at 6-h intervals until the end of the enrollment period. Withdrawal of life-sustaining therapy information is collected at any time during the study period. The schedule of activities is detailed in Table 2.

**Table 2 Tab2:** Schedule of activities

Activities	Screening/enrollment first dose	Treatment				Follow-up		
Day	1	2	3	4	5	30 (clinic)	90 (phone)	180 (clinic)
Time frame	First dose within 24 h of ICH onset							
Pre-randomization								
Diagnostic CT	X							
CTA/MRI to rule out underlying lesion	X							
Inclusion/exclusion criteria review	X							
Consent by participant or legally authorized representative	X							
MRI to rule out underlying lesion	X							
Stability CT	X							
Pregnancy test	X							
Demographics	X							

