Medical history and admission information	X							
Concomitant medications review	X							
At randomization								
Vital signs	X							
Glasgow Coma Scale	X							
Baseline (premorbid) modified Rankin Scale (caregiver interview)	X							
Post randomization								
Research MRI					X			
Usual care clinical CT		X	X	X				
Research CT					X			
Therapy intensity level	X	X	X	X	X			
National Institutes of Health Stroke Scale	X	X	X	X	X	X		X
Glasgow Outcome Scale-Extended						X	X	X
Glasgow Coma Scale	X	X	X	X	X	X		X
Montreal Cognitive Assessment					X	X		X
Stroke Impact Scale-16					X	X		X
Barthel Index	X				X	X	X	X
Modified Rankin Scale						X	X	X
EQ-5D						X	X	X
Center for Epidemiological Studies–Depression						X	X	X
Concomitant medications review		X	X	X	X	X	X	X
Plasma biomarkers	X		X		X			
Cerebrospinal fluid biomarkers	X		X		X			
Pharmacokinetic blood samples	X	X	X		X			
Dosing	X	X	X	X	X			
Adverse events assessment	X	X	X	X	X	SAE/MEOI	SAE	SAE

CT, computed tomography; CTA, computed tomography angiography; ICH, intracerebral hemorrhage; MEOI, medical event of interest; MRI, magnetic resonance imaging; SAE, serious adverse events

Secondary and exploratory safety outcomes will be analyzed using appropriate linear or logistic regression models and will account for treatment group, age, GCS score, presence of IVH, ICH volumes, the timing of drug administration, and hematoma location. No imputation of missing safety end points will be used. Instead, sensitivity analyses will be performed, whereby participants with missing secondary safety data will be assumed to have had a safety event and then not to have had a safety event. The analyses will account for the variability in dosing and treatment duration, which can range from 2 to 10 doses depending on the date of discharge. This variability will be addressed through various approaches, such as categorizing participants into dose groups, treating the number of doses as a continuous variable, and calculating area under the curve that considers the dose and duration of the doses given. The point estimate of the proportion of total safety events and corresponding two-sided 95% confidence intervals will be calculated under both extreme scenarios to provide estimates of uncertainty in the presence of these missing data. SAS, STATA 17, and/or R software will be used for statistical analysis. Statistical significance will be set at *p* < 0.05.

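### The day 30, 90 and 180 contacts are timed from the last dose, which moves with discharge by about 4 days, instead of from one fixed origin such as randomization

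*Protocol article*

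**What the plan says.** The Follow-Up Time section of the protocol article sets one rule for all later contacts. For clinic visits: "Follow-up clinic visits will be done at 30 ± 3 days and 180 ± 14 days after drug last dose". For the telephone contact: "Follow-up phone calls will be done at 90 ± 3 days after drug last dose".

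The last dose is not a fixed day. Study Intervention gives infusions "every 12 ± 2 h for up to 5 days (10 doses) or until discharge, whichever comes first", and Statistical Analyses says that dosing and treatment duration "can range from 2 to 10 doses depending on the date of discharge".

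Elsewhere the article uses other origins, or none:
- Study Outcomes lists, among the exploratory end points, "participant status at 180 days from ICH".
- Study Outcomes also says "Secondary outcomes include all-cause mortality at 30 days" and names no starting point for the 30 days.
- The functional scales are assigned to days 30, 90 and 180, again with no origin apart from the visit rule.

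On the analysis set, Statistical Analyses says: "The intention-to-treat analysis set (all randomized participants) will be used for efficacy analysis". The safety set is defined separately, as those who received any study treatment.

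**The concern.** The last dose happens after randomization, and its timing depends on how the patient does. Patients who recover quickly tend to go home early, receive fewer doses and so, under this rule, reach their day 30 and day 90 assessments sooner after the stroke than patients who stay for the whole course. Function after ICH changes with time, most quickly in the first weeks, so a clock that runs differently for early and late discharges adds noise linked to prognosis. If treatment changed length of stay, or led to infusions being stopped more often in one arm, the mean assessment time would also differ between arms.

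Two further problems follow from the wording. The 180-day contact has two origins, the last dose and the ICH. And a participant who is randomized but never dosed belongs to the efficacy set, yet has no date from which to count a visit.

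**Working it through.** **Inputs.** Dosing interval 12 h, tolerance 2 h either way, at most 5 days or 10 doses (Study Intervention). Range of 2 to 10 doses (Statistical Analyses). Windows of 3, 3 and 14 days either side of days 30, 90 and 180 (Follow-Up Time).

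**The plan's own figure.** 5 days × 24 h ÷ 12 h = 10 doses, as stated.

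**Time from first to last dose** = (number of doses − 1) × 12 h.
- 2 doses: 1 × 12 = 12 h = 0.5 days.
- 10 doses: 9 × 12 = 108 h = 4.5 days.
- Difference: 108 − 12 = 96 h = 4.0 days.

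With the 2 h tolerance the shortest 2-dose span is 10 h. Nine intervals of 14 h would give 126 h, but that is beyond the 5-day limit of 120 h. Taking 120 h as the ceiling, the largest spread is 120 − 10 = 110 h, or about 4.6 days.

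**Visit targets and windows, in days from first dose, at 12 h spacing:**

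| Contact | Target, 2 doses | Window | Target, 10 doses | Window | Window under a fixed origin |
|---|---|---|---|---|---|
| Day 30 | 30.5 | 27.5–33.5 | 34.5 | 31.5–37.5 | 27–33 |
| Day 90 | 90.5 | 87.5–93.5 | 94.5 | 91.5–97.5 | 87–93 |
| Day 180 | 180.5 | 166.5–194.5 | 184.5 | 170.5–198.5 | 166–194 |

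For a full-course participant the day 30 target (34.5) lies 1.5 days past the upper limit of 33 that a fixed origin would allow. Of that participant's 6-day window, (37.5 − 33) ÷ 6 = 75% lies beyond day 33.

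**Relative size of the 4-day shift.** 4 ÷ 30 = 13%, 4 ÷ 90 = 4%, 4 ÷ 180 = 2%.

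**What it would take to separate the arms.** Each dose of difference in the mean number given moves the mean assessment time by 12 h, or 0.5 days. The article gives no expected dose count by arm, so no arm difference can be calculated.

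**Side-by-side reading.** Follow-Up Time counts the 180-day contact from the last dose. Study Outcomes counts 180-day status from the ICH. With the first dose up to 24 h after onset and the last dose nominally up to 4.5 days after that, the two target dates can be as much as 1 + 4.5 = 5.5 days apart.

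**The case against.** The strongest reply is that this is small and touches nothing critical. Four days is 4% of 90 and 2% of 180, and at day 180 it sits well inside the 14-day tolerance. The functional scales are exploratory in a phase 2a safety trial. All of that stands, and it limits the point mainly to day 30 and, to a lesser degree, day 90.

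A reader might infer several stronger things that the article does not support:
- *That the randomized comparison is broken.* Treatment is double-blind, IV equipment is covered and follow-up coordinators are blinded. Nothing shows that dose count or length of stay differs by arm, and a difference in arm means would be smaller than the 4-day individual extreme. Blinding would not remove a shift caused by a real drug effect on recovery, so the possibility remains, but only as a possibility.
- *That 30-day mortality is distorted.* The visit rule does not define the mortality clock. Deaths have dates and can be counted from randomization whenever the visit takes place. Here the article merely omits the origin.
- *That the rule pushes follow-up past the anticipated end of data collection in June 2026.* Someone randomized on 31 December 2025 reaches day 180 on 29 June 2026 counted from randomization, but the 14-day tolerance carries that to 13 July. Both clocks can overrun, so this does not favour either.

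The never-dosed participant is also likely to be rare, since eligibility requires being able to receive the first dose within 24 h. Still, the article itself separates randomized from treated participants, so the case is foreseen and the visit rule does not cover it. Finally, the 30, 90 and 180 columns in Table 2 may be simple visit labels and are not relied on here as a further clock.

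**Conclusion.** The point holds in a limited form. This is a stated rule that conflicts with another statement in the same article, not a detail left to a fuller document. It moves assessment time by up to about 4 days between early-discharge and full-course participants, and the movement is linked to recovery. The shift exceeds the 3-day tolerance at days 30 and 90 and is minor at day 180. Mainly the exploratory functional scales are affected, most at day 30. The 7-day primary outcome is not affected.

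The size rests on 12 h dosing, on the stated range of 2 to 10 doses, and on the interval from randomization to first dose being similar across participants, which the article does not give. That early discharge reflects better recovery is a clinical expectation, not a figure in the article. An arm difference in timing is possible but not shown.

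**What to change.** In Follow-Up Time, count the 30-, 90- and 180-day contacts from randomization, keep the stated windows, and apply the rule to everyone randomized whatever number of doses they received. In Study Outcomes, name randomization as the origin for 30-day mortality and for 180-day status, so that the two sections agree.

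The cost is a wording change and an update to the visit-date calculator. Participants already followed under the present rule will have visits a few days off the new target. Their number is unknown: the article reports nine enrolled by August 2023, with recruitment planned to December 2025. For them, report the actual days from randomization to each assessment.

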### Study Outcomes

The primary study outcome is the proportion of deaths from all causes during the first 7 days post randomization. Secondary outcomes include all-cause mortality at 30 days, hematoma expansion and recurrent ICH, brain infection, standard pharmacokinetic parameters (time to maximum plasma concentration [*T*_max_], *C*_max_, area under the curve, half-life [*t*_1/2_], clearance [CL], volume of distribution during terminal phase [*V*_z_], apparent terminal elimination rate constant [λ_z_]) determined at different times after MW189 administration, radiographic measures of edema during treatment and at the end of treatment for days 1–5, and measures of plasma and cerebrospinal fluid inflammatory and neuronal injury biomarkers during treatment and at the end of treatment for days 1–5. We will use a semiautomated threshold approach (range 44–100 Hounsfield units) to determine hematoma volume. Significant hematoma expansion will be defined as an increase between baseline and any follow-up CT scan of > 6 mL or > 33%. IVH volume will not be included in hematoma expansion. Recurrent ICH refers to the emergence of a new ICH following an initial episode of spontaneous ICH. It is subsequent spontaneous bleeding in the brain distinct from the initial event, typically occurring after a time frame of around 30 days or more. This is different from ICH expansion, which involves the enlargement of the initial bleed without the occurrence of a completely new bleeding event. Brain infection refers to infection present within the brain tissue and is evaluated based on the clinical symptoms, laboratory test results, and imaging findings. Radiographic measures of edema refer to the quantitative assessment of PHE and will be analyzed via both CT and magnetic resonance imaging (MRI) scans using semiautomated volumetrics with OsiriX software to compare the volume of edema between the two treatment groups. The primary imaging outcomes are absolute PHE and relative PHE and edema extension distance measured on brain CT scans performed at admission and at day 5 of the infusion. PHE measurements on MRI will be performed on the subset with MRI at baseline and at the end of the study. Group differences in edema volumes will be compared.

Exploratory end points include clinical and functional outcomes collected at days 30, 90, and 180 (assessed using dichotomized modified Rankin Scale scores of 0–3 vs. 4–6, the National Institutes of Health Stroke Scale, the Montreal Cognitive Assessment, the Barthel Index, the Stroke Impact Scale, and the Center for Epidemiologic Studies-Depression scale) and participant status at 180 days from ICH, including serious AEs, AEs of special interest, hemorrhage expansion and recurrent ICH, infections, and mortality.

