### Patient Population

A total of 120 participants (60 per group) with acute spontaneous nontraumatic ICH are eligible for this study. The inclusion and exclusion criteria are detailed in Table 1. Written informed consent will be obtained from all participants or their legally authorized representatives.

**Table 1 Tab1:** Inclusion and exclusion criteria

Inclusion criteria: a patient will be eligible for inclusion in the study only if all of the following criteria are met:	
Confirmed diagnosis of spontaneous nontraumatic ICH	
10 mL ≤ ICH ≤ 60 mL (confirmed via diagnostic and stability CT scans using volumetric assessment)	
Participants receiving anticoagulants are eligible upon reversal and stability within 24 h after onset of ICH symptoms	
Age ≥ 18 years	
Able to receive first dose of test article (drug or placebo) ≤ 24 h after onset of ICH symptoms	
NIH Stroke Scale score ≥ 2 at randomization or Glasgow Coma Scale score ≥ 5 at randomization	
Controlled blood pressure (systolic blood pressure ≤ 160 mm Hg) at randomization	
Premorbid modified Rankin Scale score of 0–2	
Has adequate venous access	
No planned surgical intervention except external ventricular drain	
Written informed consent from the patient or legally authorized representative	
Exclusion criteria: a patient will not be eligible for inclusion in the study if any of the following criteria are met:	
Unstable hematoma defined as > 6-mL increase as compared to previous CT volume taken at least 6 h apart within 24 h after onset of ICH symptoms	
Anticipated neurosurgical evacuation by open surgery or minimally invasive surgery with or without alteplase (external ventricular drain allowed)	
Uncontrolled temperature > 38.5 °C at enrollment	
Signs of intracranial infection or emergence of a systemic infection	
Is pregnant or lactating	
Signs of liver and kidney chronic disease (i.e., creatinine > 2 mg/dL, bilirubin ≥ 3 mg/dL, receiving dialysis)	
Nonreversible bleeding diathesis	
Used any chronic immunosuppressants or chronic antiinflammatory drugs (excluding low-dose aspirin) by any route of administration within the past 7 days	
Anticipated withdrawal of life-sustaining therapies within the first week after admission	
In the opinion of the investigator, patient has any contraindication to the planned study assessments	

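### Edema is measured from the admission CT rather than the last pre-dose CT, with no stated adjustment for baseline edema, and hematoma expansion has no defined baseline: a loss of precision and a diluted safety end point, not bias

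*Protocol article*

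**What the plan says.** **Edema.** Study Outcomes names absolute PHE, relative PHE and "edema extension distance measured on brain CT scans performed at admission and at day 5 of the infusion" as the primary imaging outcomes. The only analysis statement there is "Group differences in edema volumes will be compared". It names no change score, model or baseline term.

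**Covariates.** The one covariate list beyond the mortality model, in Statistical Analyses, opens with "Secondary and exploratory safety outcomes will be analyzed using appropriate linear or logistic regression models" and says that these models "will account for treatment group, age, GCS score, presence of IVH, ICH volumes, the timing of drug administration, and hematoma location". Baseline edema is not in it.

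**Scans before dosing.** Table 1 requires hematoma volume to be "confirmed via diagnostic and stability CT scans using volumetric assessment", and Table 2 lists the stability CT among the pre-randomization activities. The mortality model already uses ICH volume from the stability scan. Table 1 also requires a participant to be "Able to receive first dose of test article (drug or placebo) ≤ 24 h after onset of ICH symptoms".

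**Hematoma expansion.** Study Outcomes states "Significant hematoma expansion will be defined as an increase between baseline and any follow-up CT scan" of more than 6 mL or more than 33%. It does not say which scan is the baseline. In Table 1 the exclusion that begins "Unstable hematoma defined as" applies only to a rise of more than 6 mL over the previous CT. It has no percentage limit.

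**The concern.** With dosing allowed up to 24 h after onset, the admission CT can precede the first dose by many hours. The drug cannot affect edema that forms in that interval. A change measured from admission therefore carries variation unrelated to treatment, which a scan closer to dosing would remove. If admission edema is not used as a baseline either, all between-patient variation in starting edema stays in the error term.

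This matters because identifying a trend in edema is a stated aim, and Sample Size Determination claims 80% power for assumed PHE differences. With 60 per arm, precision is scarce.

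For expansion, the entry rule and the end point use different thresholds. Depending on which scan is the baseline, growth that the entry rule accepts could later be scored as an on-study safety event.

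**Working it through.** **1. The plan's own figure.** The only sample-size result with enough inputs to check is the one for mortality: 10% deaths per arm, margin 12 points, one-sided 10%, power 80%.

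n = (1.282 + 0.842)² × 2 × 0.10 × 0.90 / 0.12² = 56.4, so 57 per group, as stated.

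The edema power statement cannot be checked because no difference, SD or correlation is given.

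**2. Detectable edema difference with no baseline term.** Inputs: 60 per arm and 80% power (Sample Size Determination), and two-sided 0.05 (the general significance level, assumed to apply to edema).

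(1.960 + 0.842) × √(2/60) = 0.511 SD. The t-based value is 0.516.

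**3. Gain from adjusting for baseline edema.** ANCOVA multiplies the variance by (1 − r²), so 60 per arm acts like 60/(1 − r²). The values of r are assumptions.

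| r | 1 − r² | Acts like, per arm | Detectable difference (SD) | Power at 0.511 SD |
|---|---|---|---|---|
| no baseline term | 1 | 60 | 0.511 | 80% |
| 0.3 | 0.91 | 66 | 0.488 | 84% |
| 0.5 | 0.75 | 80 | 0.443 | 90% |
| 0.7 | 0.51 | 118 | 0.365 | 97.5% |

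If ICH volume is already in the model, r must be read as the correlation that remains after allowing for it, and the gain is smaller.

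**4. Admission scan against stability scan.** This was simulated with 8,000 trials of 60 per arm. Assumed inputs in mL, as mean (SD), were: admission edema 15 (8); pre-dose growth 5 (4), the same in both arms; post-dose growth 12 (7).

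- *Bias.* With a true effect of 0, the mean estimate is −0.01 for change from admission and −0.02 for change from stability (Monte Carlo SE 0.016 and 0.014). With a true effect of −4, the means are −3.98 and −3.99. Neither scan gives bias.
- *Precision.* The SE is about 2.05 for day 5 alone, 1.46 with the admission scan and 1.28 with the stability scan. Change scores and ANCOVA agree closely.
- *Size of the switch.* 1 − 1.28/1.46 = 0.12. As a closed-form check, the error variance is 4² + 7² = 65 from admission and 7² = 49 from stability. √(49/65) = 0.868, a cut of 13%, which agrees within simulation error.

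**5. Expansion.** 33% is less than 6 mL when the starting volume is below 6/0.33 = 18.2 mL. The lower entry limit is 10 mL, so the mismatch covers starting volumes from 10 to about 18 mL.

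- Starting at 10 mL, rises above 3.3 mL and up to 6 mL pass entry but exceed 33%.
- Growth from 12 to 17 mL is +5 mL, so it passes entry, and 5/12 = +42%, so it exceeds the end-point threshold.

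Suppose a fraction q of participants has crossed the threshold before dosing and is still above it at follow-up, and later risk does not depend on this. The observed risk difference is then (1 − q) times the true post-dose difference. With q = 0.05, 0.10 or 0.20 (assumed), a true difference of 10 points appears as 9.5, 9 or 8 points.

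**The case against.** **A reader might infer that pre-dose growth is counted as treatment effect.** The documents do not support this. Allocation is 1:1 and randomized, so growth before dosing has the same distribution in both arms, and the simulation shows no bias. Chance imbalance remains possible. Only a within-arm reading of change from admission would mislead.

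**A reader might infer that the plan has chosen a covariate list for edema and left baseline edema out of it.** The list is worded for safety outcomes and does not name edema. A condensed article may leave the edema model to the SAP. Admission edema is measured, and nothing says that it will be discarded. This objection stands against any claim of a wrong model. It does not reach the choice of scan, which the article itself fixes.

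**The larger gains use a weak comparator.** The figures of 66, 80 and 118 are set against no baseline term at all, to which the article does not commit. In the simulation most of the gain comes from using any baseline scan, and the switch of scan adds about 12%. This is fair, and the two gains are kept apart here for that reason.

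**The expansion point is conditional.** The stability CT is a plausible reading of baseline, since the mortality model uses it. The stability CT is also taken before randomization, so pre-dose growth becomes an event only if a later follow-up scan still exceeds the threshold. Both objections are right. What stands is that the article leaves the scan undefined and that one natural reading produces the mismatch.

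**A reader might extend the mismatch above 18 mL**, arguing that repeat stability scans let growth accumulate. The exclusion can equally be read as applying to every pair of scans, so no such extension is claimed.

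**Conclusion.** The point holds as one of precision and definition. The article names the admission CT for edema although a later pre-dose scan exists for every participant, and it states no baseline adjustment. The randomized comparison stays unbiased.

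The cost of using no baseline term runs from slight at r = 0.3 to large at r = 0.7, and r is not in the documents. The cost of the admission scan relative to the stability scan is about 12% of the SE under the assumed inputs, and it would change with the amount and spread of pre-dose growth. All of this takes admission CT to mean the diagnostic scan, because Table 2 has no scan labeled admission.

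For expansion, the undefined baseline is certain. The dilution follows only if the baseline is the admission CT. It then concerns bleeds of 10 to about 18 mL, in a proportion that the documents do not give. It would understate a real difference in this safety end point.

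The change is worth making before unblinding, because a baseline chosen afterwards could look driven by the data.

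**What to change.** - Define baseline for PHE and for hematoma expansion as the last CT before the first dose, that is, the stability CT (the latest one if it was repeated).
- Compare day-5 absolute PHE, relative PHE and edema extension distance between arms by ANCOVA, each with its own baseline value from that scan as a covariate.
- State whether the covariate list in Statistical Analyses also applies to edema. If it does, add the baseline edema value to it.

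The cost is edema segmentation on a scan already acquired and measured for eligibility, one extra covariate, and a few lines in the SAP. Enrollment, visits, treatment and the entry criteria are untouched. A mixed model that adds the usual-care CTs of days 2–4 is not part of this change. The timing of those scans may follow the clinical course, so their use is a separate and debatable choice.
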